### Interventions

#### Sports Stars Brazil group

Sports Stars will be conducted in small groups of four or five children aged 6–12 years old, with ASD and ACSF-SC level I-II, led by one physical therapist (the same in all Sports Stars groups) with the assistance of Occupational Therapy and Physical Education undergraduate and graduate students. Each session will consist of the following activities: arrival of participants (10 minutes); warm up (5 minutes), locomotor skill training, e.g. running and jumping activities (15 minutes); object control skill training; e.g. dribbling, discus, bouncing, catching (15 minutes); modified sports game (10 minutes); and a cool down (5 minutes) [18, 31]. Participants will receive eight, one-hour, weekly sessions of Sports Stars Brazil, with two weeks focusing on each of the following popular Brazilian sports: soccer, handball, basketball and athletics, per the published protocol for children with CP [31]. The structure main components of Sports Stars Brazil, as well as the strategies for supporting the autistic children during the sessions are detailed in Fig 2. Along the program the complexity of the task is graded, aiming to improve the child’s performance and developing activity competence in each of the physical literacy domains (i.e., physical, cognitive, psychological and social skills). Standard descriptors are used to guide each child’s progress, as detailed in the Sports Stars Session Plan examples (see S2 File)”.

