*Overall Participation at home, school and community*
**Participation and Environment Measure for Children and Youth—PEM-CY:** Will be used to assess participation at home, school and community [62, 63]. The measure identifies attendance and involvement of children in activities carried out at home, at school and in the community, as well as the characteristics of these environments that influence participation in six parts: frequency of participation, involvement of participation, desire to change participation, support for the environment, support for the environment and environmental resources [64, 65]. The PEM-CY has moderate to good internal consistency and test-retest reliability indices [62] and was translated and culturally adapted for the Brazilian population [58]. The PEM-CY it has been used as an outcome measure to assess the effects of participation interventions on individuals with ASD [66, 67].

*Randomization and blinding*. Children (n = 38) will be randomized into 2 groups (Sports Stars Brazil intervention and control group). Randomization will occur when 8 to 10 the child has been recruited and the allocation ratio will be 1:1. The randomization will be performed using a computer-generated random sequence to ensure equal allocation to each group. This sequence will be used to randomize children into the immediate group, or the control group. A new sequence will be used for each subgroup randomization until 36 children are allocated, or no further participants can be recruited. All assessments will be performed before the allocation of each subgroup. Thus, the use of the block randomization method is unlikely to increase the probability of identifying the allocation of participants.

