#### Usual care or control group

Participants in the control group will receive their standard care, including maintaining existing occupational therapy and/or physical therapy intervention programs. Children with ASD in Brazil are expected to receive 1 to 2 sessions of occupational therapy (but not physical therapy) per week in public or private clinics. Both interventions provide individualized treatment plans tailored to the needs of each child. Generally speaking, physical therapy provides a general exercise program that involves gross motor training, muscle strengthening, and balance and coordination training. Occupational therapy usually involves sensory integration, neuropsychomotor development and participation in occupations (activities of daily living and education). The activities done by participants in the control group and the treatment adherence will be registered in a daily activity (see S3 File). To ensure equal access to this intervention, after they have participated in their post-intervention and follow-up assessments, participants in the control group will be invited to receive the 8-week Sports Stars Brazil intervention, but no outcomes will be collected.

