### Statistical methods

#### Sample size rationale

This study is designed to investigate the feasibility of conducting a future RCT to evaluate the effectiveness of Sports Stars and to build decision-making processes to guide the execution of a larger study, particularly concerning satisfaction, adherence. Despite of no sample size calculation is necessary in a feasibility trial, 15–20 subjects by group are suggested to determine if enrollment is sufficient to progress to a full RCT [33]. Our aim is to identify 36 potential participants to reach our target sample (18 per group) [70].

*Data analysis*. For process feasibility, participant recruitment and demographic/clinical data will be reported as means and standard deviations for continuous parametric data, medians and ranges for continuous non-parametric data, and frequencies and percentages for categorical data as per CONSORT recommendations [35]. Success criteria for feasibility will be reported descriptive and narratively, with accompanying 95% Confidence Interval (CI), when appropriate.

For scientific feasibility, as the objective of the study is to inform a definitive RCT, the analysis will focus on estimating treatment effect size and variance. No statistical significance tests (p value) or hypotheses regarding the effectiveness of the treatment will be performed. Treatment effects for secondary outcome measures will be presented as means, SD and CIs [35]. Considering a normal data distribution, effects sizes for each scientific feasibility outcome will be collected pre-intervention, immediately post intervention and at 12 weeks post intervention, using the following equation:

$$Cohen\overset{ˊ}{s}\;D=\frac{Mean\;pre-post\;change\;(treatment)-Mean\;pre-post\;change\;(control)}{\;Standard\;deviation\;(pooled)}$$

The following thresholds will be considered for interpretation of effect size: small (0.20 0.49), medium (0.50–0.79) and large (>0.80). High scores indicate better outcomes and positive effect sizes suggest benefit from Sports Stars over the control group [71]. The 95% CI will also be reported.

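### Sports Stars is delivered in about four peer groups and randomised in waves, but the planned effect size and its 95% CI have no group or wave term

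*Protocol article*

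**What the plan says.** - Delivery in the intervention arm (Sports Stars Brazil group): "Sports Stars will be conducted in small groups of four or five children aged 6–12 years old". The groups are "led by one physical therapist (the same in all Sports Stars groups" and meet weekly for eight one-hour sessions, each with a modified sports game.
- Delivery in the control arm (Usual care or control group): "Participants in the control group will receive their standard care". That care follows individual treatment plans.
- Allocation (Randomization and blinding): "Randomization will occur when 8 to 10 the child has been recruited and the allocation ratio will be 1:1".
- Size (Sample size rationale): "Our aim is to identify 36 potential participants to reach our target sample (18 per group" in a two-arm design. The number is a rule of thumb, and the rationale does not mention delivery groups.
- Analysis (Data analysis): because the study is to inform a definitive trial, "the analysis will focus on estimating treatment effect size and variance". The effect size is written out as the difference in mean pre-post change divided by a pooled SD, and "The 95% CI will also be reported". The method for the interval is not given. No group term, wave term, ICC or design effect appears anywhere in the article.

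**The concern.** This is a partially nested design: one arm is treated in peer groups and the other individually. Children who train and play together for eight weeks may change in similar ways. The protocol makes peer interaction part of the treatment, counting group delivery that motivates children to play together among the study's strengths, and some outcomes concern involvement and social competence. Having one therapist for all groups removes differences between therapists, but not differences between peer groups.

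The written formula takes each child as the unit. Its interval may therefore misstate the uncertainty of d. The variance passed on to the definitive trial would also come without the split between and within groups that is needed to size a trial of a group-delivered intervention.

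**Working it through.** **Inputs.** 18 children per arm; Sports Stars groups of 4 or 5 (mean m = 4.5); waves of 8 to 10 at 1:1, which implies one Sports Stars group and 4 to 5 controls per wave. Number of groups: 18/5 = 3.6 to 18/4 = 4.5, so about four. ICCs of 0.05, 0.10 and 0.20 are assumptions. There is no calculated sample size to reproduce; 2 × 18 = 36 agrees with the stated total. Randomization and blinding also gives a figure of 38, a separate inconsistency: 19/5 = 3.8 to 19/4 = 4.75 groups leaves the result essentially unchanged.

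**1. Independent children, d near 0.** SE(d) = √(1/18 + 1/18) = 0.333; 95% half-width 1.96 × 0.333 = 0.65.

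**2. Clustering in the Sports Stars arm only, no shared wave effect.** Design effect DE = 1 + (m − 1) × ICC; SE(d) = √((DE + 1)/18); ratio to the independent SE = √((DE + 1)/2).

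| ICC | DE | Effective n, Sports Stars arm (18/DE) | (DE + 1)/2 | SE ratio | Half-width | Simulated coverage |
|---|---|---|---|---|---|---|
| 0 | 1 | 18 | 1 | 1 | 0.65 | 95.0% |
| 0.05 | 1.175 | 15.3 | 1.09 | 1.04 | 0.68 | 93.9% |
| 0.10 | 1.35 | 13.3 | 1.18 | 1.08 | 0.71 | 92.9% |
| 0.20 | 1.70 | 10.6 | 1.35 | 1.16 | 0.76 | 90.7% |

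The simulation used 100,000 runs, groups of 4, 4, 5 and 5, 18 unclustered controls and an ordinary pooled-SD t interval.

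**3. Shared wave effects.** Let w be the share of variance due to wave effects common to both arms and g the group-specific share in the Sports Stars arm. With waves split evenly, w cancels in the difference: variance = [2 − 2w + (m − 1)g]/18, against about 2/18 for the unadjusted calculation. The unadjusted interval is too narrow only if (m − 1)g > 2w, that is g > 2w/3.5 = 0.57w. With g = 0.10 and w = 0.05 the bracket is 2 − 0.10 + 0.35 = 2.25, so the interval is too narrow. With g = 0.05 and w = 0.10 it is 2 − 0.20 + 0.175 = 1.975, so the interval is very slightly too wide.

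**4. The variance itself.** In the same simulation the mean pooled variance was 0.994, 0.990 and 0.979 of its true value at ICC 0.05, 0.10 and 0.20: understated by about 0.6%, 1% and 2%.

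**5. Consequence for a full trial.** Illustration with d = 0.5, two-sided 5% and 80% power (assumed, not from the article): 63 per arm if children are independent. Multiplying the unrounded 62.8 by (DE + 1)/2 gives 69, 74 and 85 per arm, about 9%, 18% and 35% more.

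**6. What four groups can say about the ICC.** With a true ICC of 0.10, the central 95% of simulated estimates runs from −0.25 to 0.55; with a true ICC of 0, from −0.26 to 0.42. The two can hardly be told apart.

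**The case against.** The strongest reply is that nothing in the documents shows a positive ICC and the interval method is not stated, so an interval that is too narrow is an inference. This stands. So does the point about direction: each wave feeds both arms, shared wave effects cancel, and ignoring them pushes the interval the other way (step 3).

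It is also fair that the effect is small at low ICCs, that no significance test is planned, and that the only numerical success criteria are response rate and completion, which clustering of outcomes does not touch. Process feasibility is the first aim; effect size and variance come second. A usable ICC cannot come from about four groups, and further modelling may sit in an analysis plan that is not shown.

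Three stronger readings are tempting and are not supported:
- A reader might infer that the reported variance lacks the between-group part. The SD is taken across all children in an arm, so that variation is already in it, almost in full (step 4). Only its separation is missing.
- A reader might infer that the full trial will be too small. The article does not say how that trial will be sized; the shortfall arises only if the variance is used without a design effect.
- A reader might infer that no clustering figure will exist at all. That can be said only of this article.

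What remains is that the article fixes an explicit formula which ignores both features of its own design, and that the result is meant for planning a trial of a group-delivered intervention.

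**Conclusion.** The point holds in a conditional form. The interval of d is too narrow if the group-specific ICC is positive and exceeds about 0.57 of the shared wave share of variance; otherwise it is about right or too wide. With no shared wave effect, the true standard error is about 4%, 8% or 16% larger than the unadjusted one at ICCs of 0.05, 0.10 or 0.20, and nominal 95% coverage falls to about 94%, 93% or 91%. The larger practical consequence is for the definitive trial: about 9%, 18% or 35% more children at those ICCs than the unclustered variance implies.

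These figures rest on assumed ICCs, 18 children per arm, groups of 4 to 5 and uncorrelated controls. The point is minor to moderate, a cheap improvement and not a flaw that threatens the feasibility conclusions.

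**What to change.** Add to Data analysis:

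1. Record each child's randomisation wave and Sports Stars group, and report mean change by group.
2. Keep the planned d. As a sensitivity analysis, add an interval that accounts for wave and for group in the intervention arm only.
3. Show the CI of d over assumed ICCs from 0.05 to 0.20. This will be the more informative display, because an interval that estimates the group component from four groups has about three degrees of freedom (4 − 1).
4. Report the observed ICC with its CI as descriptive only, and say that it will be very imprecise.
5. State that the full trial's sample size will apply a design effect over a range of ICCs.

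**Cost.** Analysis work only, with no change to recruitment or treatment. Some reported intervals will be wider and the ICC will be of little use on its own. A model with a group effect in one arm reveals that arm to the analyst, whereas Randomization and blinding keeps the statistician blinded until the analyses are complete. Running the nested model after the blinded main analysis is finished would protect the main results; the text should then say that the sensitivity step is unblinded.

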**Fig 2 pone.0291488.g002:**
[figure not shown]
Structure and main components of the Sports Stars intervention.

Since children with ASD may present with repetitive and stereotyped behaviors [7], support strategies based on the guidelines of the I CAN Develop Physical Literacy, carried out in partnership by the Physical Literacy Programs (PISE) and Canucks Autism Network (CAN) [68] will be used to facilitate participation during Sports Stars [69]. Specifically, during the reception, a visual schedule will be used to introduce the day’s activities, providing predictability of the session. During the sessions strategies such as giving feedback, informing about rest time, time to hydrate and time to relax will be also used, Fig 2. All these strategies will be documented through the study.

Structure of the Sports Stars intervention and the supporting strategies applied.

#### Usual care or control group

Participants in the control group will receive their standard care, including maintaining existing occupational therapy and/or physical therapy intervention programs. Children with ASD in Brazil are expected to receive 1 to 2 sessions of occupational therapy (but not physical therapy) per week in public or private clinics. Both interventions provide individualized treatment plans tailored to the needs of each child. Generally speaking, physical therapy provides a general exercise program that involves gross motor training, muscle strengthening, and balance and coordination training. Occupational therapy usually involves sensory integration, neuropsychomotor development and participation in occupations (activities of daily living and education). The activities done by participants in the control group and the treatment adherence will be registered in a daily activity (see S3 File). To ensure equal access to this intervention, after they have participated in their post-intervention and follow-up assessments, participants in the control group will be invited to receive the 8-week Sports Stars Brazil intervention, but no outcomes will be collected.

### Participant timeline

The flowchart summarizing the experimental procedures and participants is displayed in Fig 3.

**Fig 3 pone.0291488.g003:**

Study flowchart. TGMD-2: Test of Gross Motor Development-2; GAS: Goal Attainment Scaling; 10×5ST 3: 10×5 Sprint Test; MPST: Muscle Power Sprint Test; PEDI-CAT ASD: Pediatric Evaluation of Disability Inventory—Computer Adaptive; PLPQ: Physical Literacy Profile Questionnaire; PEM-CY: Participation and Environment Measure for Children and Youth.

### Statistical methods

#### Sample size rationale

This study is designed to investigate the feasibility of conducting a future RCT to evaluate the effectiveness of Sports Stars and to build decision-making processes to guide the execution of a larger study, particularly concerning satisfaction, adherence. Despite of no sample size calculation is necessary in a feasibility trial, 15–20 subjects by group are suggested to determine if enrollment is sufficient to progress to a full RCT [33]. Our aim is to identify 36 potential participants to reach our target sample (18 per group) [70].

*Data analysis*. For process feasibility, participant recruitment and demographic/clinical data will be reported as means and standard deviations for continuous parametric data, medians and ranges for continuous non-parametric data, and frequencies and percentages for categorical data as per CONSORT recommendations [35]. Success criteria for feasibility will be reported descriptive and narratively, with accompanying 95% Confidence Interval (CI), when appropriate.

For scientific feasibility, as the objective of the study is to inform a definitive RCT, the analysis will focus on estimating treatment effect size and variance. No statistical significance tests (p value) or hypotheses regarding the effectiveness of the treatment will be performed. Treatment effects for secondary outcome measures will be presented as means, SD and CIs [35]. Considering a normal data distribution, effects sizes for each scientific feasibility outcome will be collected pre-intervention, immediately post intervention and at 12 weeks post intervention, using the following equation:

$$Cohen\overset{ˊ}{s}\;D=\frac{Mean\;pre-post\;change\;(treatment)-Mean\;pre-post\;change\;(control)}{\;Standard\;deviation\;(pooled)}$$

The following thresholds will be considered for interpretation of effect size: small (0.20 0.49), medium (0.50–0.79) and large (>0.80). High scores indicate better outcomes and positive effect sizes suggest benefit from Sports Stars over the control group [71]. The 95% CI will also be reported.

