The prevalence and rate of diagnosis of children with ASD has been growing in recent years [20, 21]. According to the Brazilian Society of Pediatrics (SBP) [22], in Brazil, children with ASD frequently receive a late diagnosis and consequent delayed access to intervention, which might compromise their development [22]. There are significant advances in the international public policies for this population [20, 21]. However, in Brazil, laws were only recently introduced to guarantee the rights of people with ASD, for example to participate in sports and leisure activities (Laws: 12.764/2012–13.146/2015) [23, 24]. Despite the evidence suggesting that participation of people with ASD in leisure-time physical activities and group sports improves their socialization skills, communication, development of independence, motor skills and cardiovascular fitness, up to now, this is addressed by just one initiative by the Brazilian Government (entitled TEAtivo) [25–28]. Larger efforts are needed to developed appropriate interventions, such as Sports Stars, to improve physical activity levels and promote participation in sports and physical recreation for this population [29, 30]. However, while the effectiveness and feasibility of Sports Stars Brazil is under investigation in children with CP by our research group [31, 32], its feasibility in other conditions such as ASD is still unknown. This paper presents a feasibility Randomized clinical trial (RCT) protocol aiming to assess the feasibility of the Sports Stars Brazil intervention for children with ASD as articulated by Thabane et al. (2010) framework [33]. This framework encompasses that the aim of a feasibility study might be linked to one or more of the following four classifications: process, resources, management and scientific. In this study, we will focus on two feasibility classifications:

First, we will assess the process of feasibility that will determine the ability to enroll participants, the assessments completion rates, as well as adverse effects, satisfaction and adherence. To this purpose, a priori success criteria will be established when appropriated. Second, we will evaluate the scientific feasibility for estimating the effect size and variance of nine outcomes aligned with the fPRCs components.

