#### Outcomes

*Process and criteria for feasibility*. The process feasibility measures will include: Recruitment rates, number of patients who completed the study, as well as adherence, adverse events and satisfaction. Child’s adherence to the program will be evaluated through document analysis that will determine the number of children who started and completed the intervention. Interventionist reports on children’s behavior during the sessions and possible adverse events observed by them will also be documented. To analyze the general satisfaction of the participants, a semi-structured questionnaire adapted from Feitosa et al. [40] will be used (S1 File). This questionnaire will contain questions related to the format of the intervention, for example, satisfaction with the intervention schedule. This questionnaire also addresses the child’s interaction with the therapist, achievement of your prioritized goals. The completion of the questionnaire will be performed by the participants after the last day of the intervention.

The criteria or success for feasibility based on previous studies [41, 42] will include: ≥10% response rate from all eligible participants; and ≥80% of the participants successfully complete the study. (i.e. completed baseline, immediate and post follow up). Given the nature of the other feasibility measures they will not have cut-off criteria to determine the feasibility of performing a complete RCT. Instead, their results will be reported descriptively and will be used to determine the suitability of a full RCT combined with the others specific criteria mentioned.

This protocol study will follow one of the recommendations: not feasible, feasible with minor modifications, or feasible with closing monitoring [33].

Scientific feasibility. Preferred sports-related activity and physical activity participation goals

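### Variance is a named target for planning the full RCT but gets no interval, and the stated Cohen's d has no small-sample correction at about 18 per arm

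*Protocol article*

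**What the plan says.** The Background sets out two aims. Process feasibility comes first: "First, we will assess the process of feasibility that will determine the ability to enroll participants". Scientific feasibility comes second and is described as "estimating the effect size and variance of nine outcomes aligned with the fPRCs components".

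The Data analysis text under Statistical methods gives informing a definitive RCT as the reason for the second aim, and says "the analysis will focus on estimating treatment effect size and variance". It then fixes the presentation:

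- Treatment effects are shown as means, SDs and confidence intervals.
- Cohen's d is the difference in mean change between arms divided by a pooled SD, with cut-offs for small, medium and large.
- The effect-size paragraph closes with "The 95% CI will also be reported".
- The feasibility success criteria also get 95% intervals, where appropriate.

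No interval is attached to the SD or variance, and the d formula has no small-sample factor.

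On size, the Sample size rationale cites a rule of thumb ("15–20 subjects by group are suggested to determine if enrollment is sufficient to progress to a full RCT") and sets the target: "Our aim is to identify 36 potential participants to reach our target sample (18 per group"). The randomisation text gives a different number, "Children (n = 38) will be randomized into 2 groups", but later in the same paragraph it stops allocation at 36. The Outcomes section sets a completion criterion: "≥80% of the participants successfully complete the study".

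**The concern.** Two quantities are named as targets and only one is given a measure of precision. For planning a later trial the SD matters at least as much as d, because the required sample size is proportional to the variance. If the RCT is sized on a minimum important difference, the pilot SD is the only figure taken from this analysis, and an interval around d does not show how uncertain that SD is.

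A sample SD on about 34 degrees of freedom is imprecise, and it falls below the true SD slightly more often than above it. A planner who sees the SD without an interval has no prompt to allow for that. Separately, Cohen's d as written is biased upwards in small samples by a known factor that is easily removed.

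**Working it through.** **Is there a figure to reproduce?** There is no power or precision calculation. The target is internally consistent: 2 × 18 = 36, and 18 lies within the 15 to 20 per group of the rule of thumb.

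**Inputs from the article.** 36 children, 18 per group: df = 36 − 2 = 34. Completion at the 80% criterion: 0.80 × 36 = 28.8, about 29 children, so df = 27.

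**Assumptions not in the article.** A future two-arm RCT with 1:1 allocation, two-sided 5% test and 80% planned power; a fixed target difference; normal data; the pooled SD carrying 2n − 2 degrees of freedom. The article does not say whether its pooled SD is that of change scores or of baseline scores. The arithmetic below is the same for either.

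**Step 1: precision of the SD.** The 95% limits, as multiples of the observed SD, are √(df/χ²₀.₉₇₅) and √(df/χ²₀.₀₂₅). Implied RCT size scales with the square.

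| df | χ²₀.₉₇₅ | χ²₀.₀₂₅ | SD multiple | RCT size multiple |
|---|---|---|---|---|
| 34 | 51.97 | 19.81 | 0.81 to 1.31 | 0.65 to 1.72 |
| 27 | 43.19 | 14.57 | 0.79 to 1.36 | 0.63 to 1.85 |

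**Step 2: what happens if the point SD is carried forward.** Let r = s/σ. True power is approximately Φ((1.960 + 0.842) × r − 1.960).

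- Below 80% when r < 1: P(χ²₃₄ < 34) = 53%; with 27 df, 54%.
- Below 70% when r < (1.960 + 0.524)/(1.960 + 0.842) = 0.887, that is r² < 0.786: P(χ²₃₄ < 26.7) = 19%; with 27 df, P(χ²₂₇ < 21.2) = 22%.
- Median true power is 79% on either df. The 10th percentile is 65% with 34 df and 63% with 27.

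**Step 3: the same with a one-sided 80% upper limit.** The multiplier is √(34/26.94) = 1.12 for the SD and 34/26.94 = 1.26 for sample size (1.14 and 1.30 with 27 df). With 34 df, the chance of true power below 80% falls from 53% to 20%, and below 70% from 19% to 4%. At a standardised difference of 0.5 the RCT goes from 63 to 80 per arm.

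**Step 4: small-sample bias of d.** J = 1 − 3/(4·df − 1).

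- 34 df: J = 1 − 3/135 = 0.978, so d is too large by 1/0.978 − 1 = 2.3%, worth 1/0.978² − 1 = about 5% in RCT size.
- 27 df: J = 1 − 3/107 = 0.972, giving 2.9% and about 6%.
- At d = 0.5 with 34 df, g = 0.489 and the RCT goes from 63 to 66 per arm. If the truth were 0.489, 63 per arm would give 78.3% power.

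For scale, the 95% interval for d at 18 per arm has a half-width of about 0.66, far larger than the bias.

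Using 38 children instead of 36 changes nothing material: J = 0.979, and the chance that the SD is underestimated is 53.1%.

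**The case against.** The strongest reply is that nothing here is wrong, only absent. The SD and the number analysed will both be published, so anyone planning the RCT can compute the chi-square limit. The article never says how the RCT will be sized. Cohen's d with an interval is an accepted convention. Extra output of this kind could sit in an analysis plan that is not shown.

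Much of that stands, and it rules out several stronger readings that a reader might infer:

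- *That only the effect size gets a confidence interval.* The article also plans intervals for treatment effects and for the feasibility criteria. What lacks one is the SD.
- *That the omission makes the RCT underpowered, or more likely than not to be so.* Not printing an interval changes no one's power. The risk arises only if a point SD is carried forward, and no such commitment is made. Even then the 53% is a narrow majority, with median power about 79%.
- *That the pilot exists mainly to supply these two figures.* Process feasibility is the first aim.
- *That the uncorrected d is a serious fault.* It is worth 2% to 3%. If the RCT were sized on d itself, the chance that d exceeds its true value is 50.2% to 50.7% for true effects of 0.2 to 0.8, so the correction would not cure imprecision.

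What does not stand is the appeal to condensation. The article itself names the two targets, prints the formula and says where intervals will be given. Within that stated method, one named target is left without a measure of precision.

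**Conclusion.** A modest point that holds. Variance is one of two declared scientific-feasibility targets, and it is the one without an interval. At 34 degrees of freedom its uncertainty translates into a range of 0.65 to 1.72 times in implied RCT size (0.63 to 1.85 with 27). The consequence worth attention is the tail: about one RCT in five below 70% true power if the point SD is used, against about one in 25 with a one-sided 80% upper limit. Both figures are conditional on a planning step the article does not state and on the assumptions listed with the calculation. The missing small-sample correction is real but minor.

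**What to change.** In the Data analysis text:

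1. For each scientific-feasibility outcome, report the pooled SD with a 95% chi-square interval and a one-sided upper limit (for example 80%), and say that the upper limit will be considered in planning the full RCT alongside the point SD. The article need not bind the later trial to the upper limit; the level is a trade-off for those who design it. The chi-square limit applies to the SD only. If a baseline-to-follow-up correlation is also reported, it needs a different method.
2. Report Hedges' g, that is d × (1 − 3/(4·df − 1)), with its 95% interval, as a minor refinement.

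The cost is a few lines of text and output, with no extra children or data collection. The downsides are that g is 2% to 3% smaller than d, and that the planning figure is less favourable if the upper limit is used: about 26% more participants at 34 degrees of freedom.
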